| Randomization        | Patients were assigned in a 1:1 ratio to SOXRT arm or SOX arm by block randomization.                                                                                                                                                                                                                                                                                                                                                                                                                                                                                                                                                                                   |
| Treatment            | 
This is a multicenter, phase III clinical trial led by West China Hospital, Sichuan University. Patients will be randomly assigned to either the SOXRT arm (experimental group) or the SOX arm (control group).
 
SOXRT arm: Patients will receive one cycle of induction chemotherapy with the SOX regimen 21 days prior to radiotherapy initiation, followed by S-1-based concurrent chemoradiotherapy. After completing radiotherapy, patients will undergo three additional cycles of SOX chemotherapy, with the same dosing regimen as in the induction chemotherapy.
 
SOX arm: Patients will receive a total of six cycles of SOX chemotherapy.
 |
| Statistical Analysis | 
Categorical variables were compared with the use of Chi-squared test or Fisher' s exact test. Kaplan – Meier method was used to analyses the DFS and OS, log-rank test to assess the significance, and Cox proportional hazards model to calculate hazard ratio (HR). The median follow-up time was calculated by reverse-KM method. Statistical significance was defined as a two-side P value < 0.05.
                                                                                                                                                                                                                                                       |

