# 10 Study assessment

10.1 Effective evaluation indicators: The primary purpose is: DFS. The secondary purpose is: and OS.

10.2 Safety evaluation index: including all toxic side effects and adverse events observed during the trial.

10.3 Sample content estimation: we hypothesised that synchronous radiotherapy would result in higher DFS. with a double significance level of 0.05 and a certainty of 80%. We expect that the 3-year DFS of SOX regimen combined with simultaneous radiotherapy can be at least 8% higher than that of the chemotherapy-only group, i.e., from 70% to 78%. Based on the sample size formula for the comparison of the two sample rates, the sample size needed for this project was calculated to be 516 patients; assuming that 20% of the patients would need to be excluded from the statistics, the total number of patients that would need to be enrolled in this project would be 620.

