## 10.4 Statistical methods

All clinical data were analyzed using IBM SPSS Statistics (IBM Corp., Armonk, NY, USA. version 29.0) and R software (version 4.2.1). Categorical variables were compared with the use of Chi-squared test or Fisher's exact test. Kaplan–Meier method was used to analyses the DFS and OS, log-rank test to assess the significance, and Cox

proportional hazards model to calculate hazard ratio (HR). The median follow-up time was calculated by reverse-KM method. Statistical significance was defined as a two-side P value < 0.05.

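### Enrolling 620 with 20% excluded leaves 496 evaluable patients, not the 516 the protocol says it needs

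*Protocol*

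**What the plan says.** Protocol section 10.3 builds the enrolment figure in three steps:

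- The number needed for the analysis: "the sample size needed for this project was calculated to be 516 patients".
- The allowance: "assuming that 20% of the patients would need to be excluded from the statistics".
- The result: "the total number of patients that would need to be enrolled in this project would be 620".

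The synopsis (section 1, number of patients) repeats 620 as the size of the trial. The protocol gives no other loss rate, rounding rule or allowance, and no formula for the step from 516 to 620.

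**The concern.** An allowance for losses exists so that the required number is still there after the losses have occurred. The patients lost are a fraction of those enrolled, so the required number has to be divided by the fraction retained. Multiplying it by one plus the loss rate always gives too small a figure, and 620 looks like the product of that multiplication.

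If so, the trial can recruit exactly to target, lose exactly the proportion it planned for, and still fall short of its own evaluable number. The same step would carry over into any later recalculation of the sample size, with a larger gap if the base number grows.

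**Working it through.** **Inputs, all from the protocol**

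- Evaluable number 516, exclusion rate 20%, enrolment 620: section 10.3.
- 3-year DFS 70% versus 78%, 80% power, and the method "Based on the sample size formula for the comparison of the two sample rates": section 10.3.
- Two-sided 5% level: section 10.3, and again in section 10.4, "Statistical significance was defined as a two-side P value < 0.05".
- 1:1 allocation: synopsis, randomization.

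**Reproducing 620**

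516 × (1 + 0.20) = 619.2, rounded up to 620. This matches the protocol.

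**What a 20% loss requires**

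Enrolled = needed / (1 − loss) = 516 / 0.80 = 645. Equal arms need an even number, so 646. Either is 25 to 26 more than 620, too far to be rounding.

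**What 620 delivers**

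- Evaluable after a 20% loss: 620 × 0.80 = 496.
- Shortfall: 516 − 496 = 20 patients, or 20 / 516 = 3.9% of the required number.
- Largest loss that still leaves 516: 1 − 516/620 = 16.8%.

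**Effect on power**

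With n per arm, p₁ = 0.70, p₂ = 0.78 and mean rate 0.74, the two-rate formula gives

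power = Φ{ [0.08 √n − 1.96 √(2 × 0.74 × 0.26)] / √(0.70 × 0.30 + 0.78 × 0.22) } = Φ{ [0.08 √n − 1.216] / 0.618 }.

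| Evaluable, total | n per arm | Power |
|---|---|---|
| 516 | 258 | 54.5% |
| 496 | 248 | 52.8% |

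The difference is 1.6 percentage points before rounding (54.46% − 52.84%). A log-rank approximation gives nearly the same picture. It uses the implied hazard ratio ln 0.78 / ln 0.70 = 0.697 and an average 3-year event probability of 26%, and power is 55.3% at 516 and 53.7% at 496.

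**Keeping the base number separate**

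Both powers are far below 80% because 516 itself does not follow from the stated inputs. The same formula needs 471 per arm, 942 in total, for 80% power. That is a different defect, and correcting the allowance does not cure it. The allowance step still matters once the base is corrected: 942 × 1.2 = 1,130.4 (1,131), whereas 942 / 0.8 = 1,177.5 (1,178), a gap of 47 patients.

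**The case against.** The protocol does not say what the 20% is a percentage of. The clause follows directly on the figure of 516. If 20% of 516 (103.2 patients) is added on top, 620 is right and about 516 remain. The English is loose in places, so this reading cannot be ruled out. It is strained, however: patients can be excluded from the statistics only after they have been enrolled, so the natural base is those enrolled. Even on the other reading the expected exclusion rate is 16.8% of those enrolled, and the text would need to say so.

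The effect is also small. The 20% is an assumption without stated support, 16.8% may well lie within its uncertainty, and the problem with 516 is much larger. All of this stands, and it limits the weight of the point without removing it.

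Finally, the planned analysis is Kaplan–Meier, log-rank and Cox. Patients lost to follow-up contribute time until they are censored, and power depends on events, so a power based on a head count of 496 is approximate. That is fair, although section 10.3 speaks of exclusion from the statistics rather than censoring and bases its own calculation on two rates.

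**Conclusion.** The figures in section 10.3 are inconsistent as written. At the stated 20% exclusion, 620 enrolled gives 496 evaluable patients, 20 below the stated requirement, and the enrolment consistent with both 516 and 20% is 645 (646 for equal arms). This rests on one assumption, that the 20% refers to patients enrolled, which is the ordinary sense of the sentence.

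The error is certain on that reading and modest in effect, under 2 percentage points of power. It should be corrected, but the shortfall from 80% power should not be attributed to it.

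**What to change.** Restate section 10.3 so that the three figures agree, in one of these ways:

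- Keep 620 and 20%: state that 496 evaluable patients are expected and give the matching power, about 53% on the two-rate formula with the protocol's own rates.
- Keep 620 and 516: state that 620 covers a loss of 16.8%, and say why that rate is expected, so that it is not simply fitted to the enrolment figure.
- Keep 516 and 20%: enrolment becomes 645, or 646 for equal arms, and the number in the synopsis changes with it.

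The first two need only a change of text in section 10.3 and no extra patients. The third adds 25 or 26 patients. It is sensible to do this together with a recalculation of 516, dividing the corrected base by 0.8 and naming patients enrolled as the base of the 20%.

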## 10.4 Statistical methods

All clinical data were analyzed using IBM SPSS Statistics (IBM Corp., Armonk, NY, USA. version 29.0) and R software (version 4.2.1). Categorical variables were compared with the use of Chi-squared test or Fisher's exact test. Kaplan–Meier method was used to analyses the DFS and OS, log-rank test to assess the significance, and Cox

proportional hazards model to calculate hazard ratio (HR). The median follow-up time was calculated by reverse-KM method. Statistical significance was defined as a two-side P value < 0.05.

## **11 Study Treatment Controls and Assurance**

### **11.1 Quality control measures:**

- (1) All investigators should enrol and treat patients in strict accordance with the trial plan.
- (2) The grading of all toxic reactions should be judged according to the grading criteria specified in the trial.
- (3) The outlining of the radiotherapy target area, and the preparation requirements before radiotherapy, etc. should be carried out in strict accordance with the provisions of Oncology Radiotherapy.
- (4) Inform the subjects of the possible adverse reactions during the trial, and the treatment methods to be adopted in case of adverse reactions.

### **11.2 Quality assurance measures:**

- (1) The person in charge of the study strengthens the quality supervision of this trial.
- (2) The radiotherapy target area of patients should be carried out in strict accordance with the target area outlining specifications of this study to ensure the consistency of the radiotherapy target area.
- (3) The person in charge of the study is responsible for supervising and ensuring that the rights and interests of the subjects in the clinical trial are safeguarded, that the trial records and reported data are accurate, complete and error-free, and that the trial follows the approved study protocol and relevant regulations.

## **12 Ethical requirements**

This clinical trial will be conducted in accordance with the Helsinki (2002 version) and China's relevant clinical trial research norms and regulations. The trial protocol will be approved and ratified by the Ethics Committee of West China Hospital of Sichuan University before the start of the trial. Before each patient is enrolled in the study, it is the responsibility of the investigating physician to provide him/her or his/her designated representative with a complete and comprehensive description of the purpose, procedures, and possible risks of the study in written text. Patients should be made aware of their right to withdraw from this study at any time. A written Patient Informed Consent form (included as an appendix to the protocol) shall be given to each patient prior to enrolment and it is the responsibility of the investigating physician to obtain informed consent prior to enrolment of each patient in the

study.

### **13 Appendix 1: Common Toxicity Criteria for Adverse Events (CTCAE) of the US National Cancer Institute (version 4.0)**

The Common Terminology Criteria for Adverse Events (CTCAE) Version 4.0, developed by the U.S. National Cancer Institute (NCI), provides a standardized framework for assessing and grading the severity of adverse events (AEs) in oncology clinical trials and patient management. The complete CTCAE v4.0 document is available

at:[https://ctep.cancer.gov/protocolDevelopment/electronic\\_applications/ctc.htm#ctc\\_archive](https://ctep.cancer.gov/protocolDevelopment/electronic_applications/ctc.htm#ctc_archive)

### **Contour Delineation Specifications for Postoperative Radiotherapy Target Volumes in Gastric Cancer**

The delineation of postoperative radiotherapy target volumes after D2 radical gastrectomy for gastric cancer primarily refers to the delineation of the CTV (Clinical Target Volume). Substantial differences may exist in target volume delineation across institutions and among clinicians. This may affect the quality of multicenter clinical studies. Therefore, this contouring specification is formulated to improve the consistency of radiotherapy planning in this clinical study.

#### **I. Radiotherapy Simulation**

Contrast-enhanced CT simulation is used. Patients should fast for 4 hours before simulation; the position should be supine, with both arms elevated (hands holding the elbows), immobilized with a body mold; the scanning range should extend from the inferior border of T6 to the inferior border of L4, with a slice thickness of 3 mm.

#### **II. CTV Delineation**

1. Postoperative radiotherapy target volumes for gastric cancer include the tumor bed, anastomosis, and regional lymph nodes. On each slice of the simulation CT images, the regions requiring radiotherapy should be delineated within a single CTV; that is, each region should not be contoured separately.

(1) Anastomosis:

- ① For distal one-third gastric cancer, the duodenal stump should be included in the CTV;
- ② For proximal one-third gastric cancer or tumors at the esophagogastric junction, the esophagojejunostomy should be included in the CTV;
- ③ For tumors at the esophagogastric junction, the CTV should extend cranially to include 4 cm of the esophagus (to cover paraesophageal lymph nodes).

(2) Tumor bed

- ① For gastric cancer with T stage T1-2, the CTV does not need to include the tumor bed;
- ② Anterior abdominal wall: only in gastric cancer with T stage T3-4, when preoperative imaging and/or the intraoperative surgeon's description indicates suspected or confirmed invasion of the anterior abdominal wall, or an indistinct interface between the tumor and the anterior abdominal wall, should the postoperative radiotherapy CTV include the anterior abdominal wall.

### (3) Lymphatic drainage regions

The regional lymph nodes to be included in the CTV vary according to the anatomic location of the gastric cancer (proximal one-third, middle one-third, and distal one-third stomach).

- ① Esophagogastric junction cancer, cardia cancer, or upper one-third gastric cancer: paraesophageal lymph nodes, paracardial lymph nodes (stations 1-2), lymph nodes along the lesser and greater curvatures (stations 3-4), lymph nodes along the left gastric artery (station 7), lymph nodes along the celiac artery (station 9), and lymph nodes along the splenic artery / splenic hilar region (stations 10-11). (Stations 1-4, 7, 9-11)
- ② Middle gastric cancer (gastric body cancer): paracardial lymph nodes (stations 1-2), lymph nodes along the lesser and greater curvatures (stations 3-6), lymph nodes along the left gastric artery (station 7), lymph nodes along the common hepatic artery (station 8), lymph nodes along the celiac artery (station 9), lymph nodes along the splenic artery / splenic hilar region (stations 10-11), hepatoduodenal ligament lymph nodes (station 12), and lymph nodes in the posterior pancreaticoduodenal region (station 13). (Stations 1-13)
- ③ Gastric antrum / distal one-third gastric cancer: lymph nodes along the lesser and greater curvatures (stations 3-6), lymph nodes along the left gastric artery (station 7), lymph nodes along the common hepatic artery (station 8), lymph nodes along the celiac artery (station 9), lymph nodes along the splenic artery (station 11), hepatoduodenal ligament lymph nodes (station 12), and lymph nodes in the posterior pancreaticoduodenal region (station 13). (Stations 3-9, 11-13)

Note: When the extent of primary tumor invasion involves more than one anatomic region, the radiotherapy CTV should also include the corresponding lymphatic drainage regions.

### **III. Radiotherapy Planning**

1. 3D-CRT, IMRT should be used;
2. Based on the CTV, the PTV should be expanded by 0.8 cm in the anterior, posterior, left, and right directions, and by 1.0 cm in the cranial-caudal direction;
3. Minimum dose covering 95% of the PTV: 50.4 Gy in 28 fractions; hotspot dose  $\leq$  107% of the prescription dose, with hotspot volume  $\leq$  2 cc;
4. Conformity index (CI)  $\geq$  0.8;
5. Dose constraints for major organs at risk: spinal cord  $\leq$  40 Gy, liver V30  $\leq$  33%, the dose to 33% of the volume of one kidney (most commonly the right kidney)  $<$ 15 Gy, mean dose to both kidneys  $<$ 15 Gy; small bowel D50  $<$ 20-30 Gy.
